## Abstract

**Background:**

Post-exposure prophylaxis (PEP) is a well-established strategy for the prevention of infectious diseases, in which recently exposed people take a short course of medication to prevent infection. The primary objective of the COVID-19 Ring-based Prevention Trial with lopinavir/ritonavir (CORIPREV-LR) is to evaluate the efficacy of a 14-day course of oral lopinavir/ritonavir as PEP against COVID-19 among individuals with a high-risk exposure to a confirmed case.

**Methods:**

This is an open-label, multicenter, 1:1 cluster-randomized trial of LPV/r 800/200 mg twice daily for 14 days (intervention arm) versus no intervention (control arm), using an adaptive approach to sample size calculation. Participants will be individuals aged > 6 months with a high-risk exposure to a confirmed COVID-19 case within the past 7 days. A combination of remote and in-person study visits at days 1, 7, 14, 35, and 90 includes comprehensive epidemiological, clinical, microbiologic, and serologic sampling. The primary outcome is microbiologically confirmed COVID-19 infection within 14 days after exposure, defined as a positive respiratory tract specimen for SARS-CoV-2 by polymerase chain reaction. Secondary outcomes include safety, symptomatic COVID-19, seropositivity, hospitalization, respiratory failure requiring ventilator support, mortality, psychological impact, and health-related quality of life. Additional analyses will examine the impact of LPV/r on these outcomes in the subset of participants who test positive for SARS-CoV-2 at baseline. To detect a relative risk reduction of 40% with 80% power at *α* = 0.05, assuming the secondary attack rate in ring members (*p*_0_) = 15%, 5 contacts per case and intra-class correlation coefficient (ICC) = 0.05, we require 110 clusters per arm, or 220 clusters overall and approximately 1220 enrollees after accounting for 10% loss-to-follow-up. We will modify the sample size target after 60 clusters, based on preliminary estimates of *p*_0_, ICC, and cluster size and consider switching to an alternative drug after interim analyses and as new data emerges. The primary analysis will be a generalized linear mixed model with logit link to estimate the effect of LPV/r on the probability of infection. Participants who test positive at baseline will be excluded from the primary analysis but will be maintained for additional analyses to examine the impact of LPV/r on early treatment.

**Discussion:**

Harnessing safe, existing drugs such as LPV/r as PEP could provide an important tool for control of the COVID-19 pandemic. Novel aspects of our design include the ring-based prevention approach, and the incorporation of remote strategies for conducting study visits and biospecimen collection.

**Trial registration:**

This trial was registered at www.ClinicalTrials.gov (NCT04321174) on March 25, 2020.

**Supplementary Information:**

The online version contains supplementary material available at 10.1186/s13063-021-05134-7.

Role of sponsor {5c}	The study funders, including those providing in-kind support for the trial, have no role in the study design; collection, management, analysis, and interpretation of data; writing of the report; and the decision to submit the report for publication. The sponsor-investigator for this trial is also the Principal Investigator, and as such is primarily responsible for the study design; collection, management, analysis, and interpretation of data; writing of the report; and the decision to submit the report for publication. The Steering Committee will have ultimate authority over all of these activities.

## Introduction

### Background and rationale {6a}

The lack of population immunity to SARS-CoV-2, potential for pauci-symptomatic and asymptomatic transmission, basic reproductive number of roughly 2.5 [1], case fatality estimates of up to 7.2% [2], and lack of evidence-based therapies mean that the prevention of new COVID-19 cases is critical to controlling the pandemic. Encouragingly, highly effective preventive vaccines have been developed and are already being distributed in settings worldwide [3, 4]. However, the high transmissibility of the pathogen and the many implementation challenges in achieving high vaccine coverage mean that combination approaches to COVID-19 prevention will remain important in the future. Post-exposure prophylaxis (PEP) is a well-established strategy for the prevention of infectious diseases such as HIV, in which recently exposed people take a short course of medication to prevent infection. COVID-19 PEP has been identified early as a research priority by the World Health Organization (WHO) [5].

Several lines of evidence suggest that the antiretroviral lopinavir/ritonavir (LPV/r, marketed in Canada as Kaletra™) is one drug that may have meaningful antiviral activity against coronaviruses such as SARS-CoV-2, which causes COVID-19. Molecular data show that LPV/r has activity against the SARS-CoV protease M^pro^ [6], while in vitro and animal data show that it has activity against the closely related Middle East respiratory syndrome coronavirus (MERS-CoV) [7]. A small observational study in South Korea suggested that LPV/r PEP decreased the risk of infection in healthcare workers exposed to MERS-CoV [8].

An initial clinical trial in China found no definite treatment benefit of LPV/r in hospitalized COVID-19 patients [9] but was underpowered for the primary endpoint of mortality, and initiation of LPV/r was late in the course of COVID-19 disease. There was also a potential for imbalance in baseline characteristics (higher viral load, later presentation, more severe illness in the LPV/r arm) to influence the outcomes. Secondary endpoints hinted at potential benefit (numerically lower mortality, shorter ICU/hospital stay) [9]. As noted by many observers [10–14], the results underscore the need for more LPV/r trials. While subsequent results from the SOLIDARITY and RECOVERY trials showed no impact of treatment with LPV/r on mortality in hospitalized COVID-19 patients [15, 16], data are lacking on the impact of this drug when used for prophylaxis or pre-emptive therapy.

The safety of LPV/r is already well-established, since it has been widely used in HIV treatment and PEP for over 20 years [17–19]. While it can cause temporary gastrointestinal side effects [20–23], discontinuation due to side effects was uncommon in HIV PEP trials [24–26]. Drug interactions are well understood [27], although the large number of potential interacting agents can pose clinical challenges. LPV/r is safe in pregnancy, liver disease and at all levels of renal function including dialysis and is available in liquid form to facilitate use in children and adults who cannot take pills/tablets [27]. It is also available worldwide, including in resource-limited settings. Thus, the feasibility of LPV/r as COVID-19 PEP is high if shown to be effective, and it is critical to develop evidence regarding its use.

This trial will examine the efficacy and safety of a 14-day course of LPV/r as PEP in close contacts of individuals with confirmed SARS-CoV-2 infection. All items in the WHO trial registry data set can be found in the protocol (Appendix A).

### Objectives {7}

The primary objective of this trial is to evaluate the efficacy of a 14-day course of oral LPV/r as PEP against microbiologically confirmed COVID-19 among individuals with a significant unprotected exposure to a confirmed case.

Secondary objectives are

To compare the following secondary outcomes between study arm:Adverse events as defined by the DAIDS Table for Grading the Severity of Adverse Events [28];Symptomatic COVID-19 disease;Seroconversion;Hospitalization;Respiratory failure requiring (i) non-invasive or (ii) invasive ventilationMortality;Short-term psychological distress associated with COVID-19 exposure;Long-term psychological distress associated with COVID-19 exposure; andHealth-related quality of life.2.To compare clinical outcomes associated with early LPV/r treatment among participants with baseline COVID-19 infection.3.To characterize key transmission-related epidemiologic parameters among exposed contacts in a Canadian context, including exposure histories, cluster size, secondary attack rate (p_0_, incidence proportion), time to first viral shedding and burden, risk factors for transmission, and correlates of symptomatic disease.

### Trial design {8}

The COVID-19 Ring-based Prevention trial with Lopinavir/ritonavir (CORIPREV-LR) is an open-label, cluster-randomized trial of lopinavir/ritonavir versus no intervention for preventing microbiologically confirmed SARS-CoV-2 infection in high-risk close contacts of confirmed COVID-19 cases. The CORIPREV trial will use an adaptive approach to the selection of study drug, with consideration of switching to an alternative promising agent after interim analyses are completed and/or considering external data.

The trial will use a ring-based approach to delivering these preventive strategies, adapting a novel cluster trial design recently used in the 2013–16 West African Ebola epidemic in the *Ebola ça suffit*! trial [29, 30]. The approach is to define a ‘ring’ of exposed contacts around COVID-19 cases, and to randomize rings (i.e., clusters) to study drug or control (no study drug) [31]. This design maximizes statistical power by recruiting those at highest risk. It also has the potential to create a buffer of protected people around cases, such that if the drug works for prevention, the trial itself may limit transmission. Further, some COVID-19 cases may lead to “super-spreading” events [32, 33]; this variability is taken into account by defining index cases, rather than exposed contacts, as the unit of randomization. Ring vaccination has been a key part of the successful eradication of other highly transmissible infectious diseases such as smallpox [34].

## Methods: participants, interventions, and outcomes

### Study setting {9}

Initially, the trial will enroll community-based participants in Toronto, Ottawa, Montreal, and Vancouver, Canada. Study staff will be based at academic hospital sites but will conduct the majority of study visits remotely (via video-link or telephone), as per the schedule of events provided below. Additional sites may be opened in other cities depending on the degree of epidemic activity.

### Eligibility criteria {10}

Inclusion criteria for the trial are as follows:
Within the past 1–7 days, high-risk close contact with a confirmed COVID-19 case. If the index case was symptomatic, this contact must have occurred during their symptomatic period, including 1 day before symptom onset. If the index case was asymptomatic, this contact must have occurred within 14 days of the index case’s first positive SARS-CoV-2 test. High-risk close contact is defined as any of the following exposures without the consistent appropriate use of recommended personal protective equipment (e.g., face mask):
Provided direct care for the index case;Had close direct physical contact with the index case;Lived with the index case;Had close indoor contact (within 2 m), with or without direct physical contact, for at least 1 h; andHad direct contact with infectious body fluids, including oral secretions, respiratory secretions, or stool.This definition is in accordance with the definition of a high-risk close contact for COVID-19 set out by the Public Health Agency of Canada [35].

2.Successfully contacted by the study team within 24 h of study team notification of the relevant index COVID-19 case. This time window is necessary because the efficacy of PEP may be dependent on the timing of its initiation, and because randomization of a ring cannot be delayed while awaiting response from contacts that cannot be rapidly reached.3.Age ≥ 6 months, since the safety and pharmacokinetic profiles of LPV/r in pediatric patients below the age of 6 months have not been established.4.Ability to communicate with study staff in the language(s) of the study site

Exclusion criteria are as follows:
Known hypersensitivity/allergy to lopinavir or ritonavir.Current use of LPV/r for the treatment or prevention of HIV infection.Receipt of LPV/r in the context of this trial or any other trial of COVID-19 PEP within 2 days or less prior to the last known contact with the index COVID-19 case. The 2 day time window is intended to ensure that exposure would not have occurred in the presence of clinically relevant drug levels (five times the elimination half-life of LPV/r, which is estimated at 4–6 h with prolonged use).Currently breastfeeding an infant, due to potential for serious adverse reactions in nursing infants exposed to variable levels of LPV/r in breastmilk.Concomitant medications with prohibited drug interactions with LPV/r that cannot be temporarily suspended/replaced (see full study protocol in Appendix A) [27].Already known to be infected with SARS-CoV-2.Receipt of any doses of any locally licensed COVID-19 vaccine.

Enrolled participants whose baseline samples are positive for COVID-19 will continue all study procedures (including study drug) but be excluded from the primary analysis and included instead in the secondary analysis regarding LPV/r as early treatment.

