### Relevant concomitant care permitted or prohibited during the trial {11d}

Use of LPV/r together with medications cleared through cytochrome P450 3A (CYP 3A) can lead to elevated plasma concentrations of the concomitant medication. LPV/r also induces glucuronidation which may affect the exposure of some drugs. Medications that inhibit or induce CYP3A may increase or decrease serum concentrations of LPV/r, respectively. These drug-drug interactions may lead to adverse reactions, loss of therapeutic effect of the concomitant medication, and/or loss of antiviral activity of LPV/r.

Site investigators must therefore review concomitant medications at the time of enrollment. A full list of contraindicated medications appears in the study protocol in Appendix A [37], and the use of any of these products that cannot be substituted during the study dosing period is an exclusion criterion for the study. For other medications and/or supplements that are not on the list of contraindicated medications, site investigators must assess the risk of drug-drug interactions, and adjust medication doses accordingly. Study pharmacists with extensive experience with LPV/r use will provide advice to investigators regarding the management of drug-drug interactions as needed, via email or telephone consultation.

Co-enrollment into other regulated clinical trials of COVID-19 prevention is permitted, but details of the co-intervention must be documented under the concomitant medication section or other suitable part of the database.

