To date, several clinical trials of COVID-19 PEP have already been completed and reported. An initial team of American and Canadian investigators randomized 821 asymptomatic adults who reported a household or occupational exposure to someone with COVID-19 within the preceding 4 days, to receive either hydroxychloroquine or placebo, and noted no statistically significant difference in the incidence or either laboratory-confirmed COVID-19 or a compatible illness over the subsequent 14 days [61]. A shortcoming of this trial was that the availability of microbiologic testing for outcome ascertainment was limited, such that infection was confirmed by polymerase chain reaction in only 14% of participants with symptomatic disease. Our trial will overcome this limitation by using specimen self-collection, and testing of these samples within 24 h for SARS-CoV-2. Two subsequent trials of hydroxychloroquine as COVID-19 PEP have similarly shown no impact of that drug on acquisition of SARS-CoV-2 infection, using microbiologically confirmed infection by PCR as the primary outcome [78, 79].

Another novel feature of our trial design is our inclusion of baseline testing for COVID-19 in all participants. This approach will further allow us to explore the impact of lopinavir/ritonavir in the early treatment of COVID-19, since those who test positive at baseline will continue all study activities. Despite high-quality trials demonstrating that lopinavir/ritonavir is not effective as treatment in hospitalized COVID-19 patients, questions about its efficacy in early-stage treatment and prophylaxis remain unanswered. Only one other clinical trial is examining the efficacy of lopinavir/ritonavir as COVID-19 PEP, using an individual-randomized design [80].

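### Neither the LPV/r exclusion nor the co-enrolment rule keeps LPV/r from another COVID-19 PEP trial out of the control arm

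*Protocol article*

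**What the plan says.** All references are to the Protocol article.

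- **Eligibility criteria {10}, exclusions.** Receipt of LPV/r in this trial or any other COVID-19 PEP trial excludes a person if it occurred "within 2 days or less prior to the last known contact with the index COVID-19 case". The reason given is "The 2 day time window is intended to ensure that exposure would not have occurred in the presence of clinically relevant drug levels". The only exclusion for present use is "Current use of LPV/r for the treatment or prevention of HIV infection".
- **Eligibility criteria {10}, inclusions.** The qualifying exposure is "Within the past 1–7 days, high-risk close contact with a confirmed COVID-19 case", so days can pass between the last contact and enrolment.
- **Criteria for discontinuing or modifying allocated interventions {11b}.** A participant already on study drug cannot re-enrol when named in a second ring. This concerns rings of this trial.
- **Relevant concomitant care {11d}.** "Co-enrollment into other regulated clinical trials of COVID-19 prevention is permitted", on condition that "details of the co-intervention must be documented under the concomitant medication section or other suitable part of the database". Trials that test LPV/r are not excepted.
- **Discussion.** "Only one other clinical trial is examining the efficacy of lopinavir/ritonavir as COVID-19 PEP"; it is individually randomised, and its location is not given.
- **Blinding {17a} and the section on non-adherence and missing data {20c}.** The trial is open-label, and the primary analysis is by intention-to-treat.

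**The concern.** The comparison is LPV/r against no intervention, so it depends on controls not taking LPV/r during the 14 days in which the primary outcome is counted. The rules leave two ways in.

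1. **At entry.** The washout looks backwards from the last contact and stops there. Drug started between the last contact and randomisation falls outside it, and starting after exposure is the usual order of events in PEP.
2. **After randomisation.** A control knows the allocation and may join another prevention trial, including one that supplies LPV/r.

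The two routes act differently. People who enter already on LPV/r are spread evenly over the arms in expectation, because consent precedes ring randomisation. They only dilute the contrast. Co-enrolment after randomisation can differ by arm, because allocation is then known. In both cases the primary estimate moves towards no effect, and an intention-to-treat analysis keeps these people where they were allocated.

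Detection is also uneven. Lopinavir levels are measured only in a random subset of the active arm (Strategies to improve adherence {11c}), so LPV/r use by controls would be known only from what they report.

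**Working it through.** **Step 1. Trace one contact through the rules.** Take screening as day 0, last contact on day -5, and LPV/r started in another COVID-19 PEP trial on day -3 and still being taken.

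- Exposure within the past 1–7 days: met.
- LPV/r in the 2 days before the last contact (days -7 to -5): none, so this exclusion does not apply.
- Current LPV/r use for HIV: no, so this exclusion does not apply.
- Bar on people already taking study drug {11b}: it governs a second ring of this trial, so it does not apply.

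The person is eligible and may be allocated to no intervention while taking LPV/r. Someone already on LPV/r at the last contact is caught by the 2-day rule, so the gap is limited to drug started after that contact.

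The length of the window is not at fault. Five half-lives of 4–6 h are 5 × 4 = 20 h to 5 × 6 = 30 h, which is under 48 h.

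**Step 2. Reproduce the planned size.** Inputs from the Abstract and Sample size {14}: control risk 15%, relative risk reduction 40% (so 0.15 × 0.60 = 9% on LPV/r), 80% power, alpha 0.05 (taken as two-sided), 5 contacts per ring, ICC 0.05, 10% loss to follow-up.

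- Design effect: 1 + (5 − 1) × 0.05 = 1.2.
- Two-proportion formula with unpooled variance: 456.5 per arm; 456.5 × 1.2 = 547.9; divided by 5 = 109.6 rings.
- With pooled variance: 460 per arm; 460 × 1.2 = 552; divided by 5 = 110.4 rings.
- Loss to follow-up: 2 × 110 × 5 = 1100; 1100 / 0.9 = 1222.

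The stated 110 rings per arm and about 1220 enrollees reproduce. The calculation allows for loss to follow-up only, so it assumes that no control takes LPV/r.

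**Step 3. Let a share c of controls take LPV/r with the full assumed effect.** The documents give no value for c; the values below are assumptions.

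- Control risk: p_c = 0.15 × (1 − 0.4c).
- Observed relative risk: 0.09 / p_c.
- Effective number per arm: 110 × 5 / 1.2 = 458.3.
- Power: Φ{[(p_c − 0.09)√458.3 − 1.96√(2p̄(1 − p̄))] / √(p_c(1 − p_c) + 0.09 × 0.91)}, where p̄ is the mean of p_c and 0.09.

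| c (assumed) | Control risk | Observed RR | Power | Rings per arm for 80% power |
|---|---|---|---|---|
| 0% | 15.0% | 0.600 | 79.9% | 111 |
| 2% | 14.88% | 0.605 | 78.5% | 115 |
| 5% | 14.7% | 0.612 | 76.2% | 121 |
| 10% | 14.4% | 0.625 | 72.1% | 134 |

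The last column uses the pooled formula rounded up, which is why its first row is 111 and not 110.

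**Step 4. What these shares require.** If the other trial allocates 1:1 (an assumption), half of those who join it receive LPV/r. If co-enrolment were the only route, c = 5% would need about 10% of controls to join, and c = 10% about 20%.

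**The case against.** The strongest case on the other side is that this will seldom happen and that co-enrolment was a deliberate choice. The article knows of one other LPV/r PEP trial, while this trial starts in four Canadian cities. Concomitant medication is reviewed at enrolment and recorded at baseline and days 7 and 14 (Table 1), so reported use would be seen and could feed a sensitivity analysis. Any bias runs towards no effect, so it could not create a false claim of efficacy. The full protocol in the article's Appendix A is not shown and may bar concurrent LPV/r.

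Much of this stands, and it keeps the point modest. It does not remove it. The exclusion itself names other COVID-19 PEP trials, so such people were foreseen. Recording use is not a rule that excludes it, and a sensitivity analysis does not restore the primary contrast.

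A reader might also infer more than the documents support:

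- **That current users who enter would be unbalanced between arms.** Consent precedes randomisation, so they are balanced in expectation.
- **That any co-enrolment dilutes the effect as LPV/r would.** Explanation for the choice of comparators {6b} says that no agent has definitive proof of preventive efficacy, and the Discussion reports that hydroxychloroquine PEP trials showed no effect. Only LPV/r is shown to be a direct threat to the contrast.
- **That the window should run from the first contact.** A person who stopped LPV/r more than 2 days before the last contact still has a qualifying exposure free of drug. Intervention description {11a} also times drug start from the latest exposure.
- **That the vaccine exclusion ("Receipt of any doses of any locally licensed COVID-19 vaccine") should cover investigational vaccines.** No harm is quantified, prior receipt is balanced by randomisation, and participants in a blinded vaccine trial may not know what they received.

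**Conclusion.** The point holds in a limited form. As written, the rules let a person taking LPV/r from another PEP trial be randomised to no intervention, and let an open-label control join a trial that supplies LPV/r before day 14. The section on multiple rings {11b} closes this only for the trial's own drug.

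The size depends on uptake, which is not given and is probably small. Under the plan's own 15% control risk and 40% effect, each 5% of controls on fully effective LPV/r costs about 4 percentage points of power (79.9% to 76.2% to 72.1%) and moves the relative risk from 0.60 to about 0.61 and then 0.625. Partial courses would dilute less. The planned sample size is correct on its stated inputs.

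It is worth correcting because the change is a matter of wording, while contamination cannot be undone once the data are in.

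**What to change.** Reconcile Eligibility criteria {10}, the multiple-ring rule in {11b} and the co-enrolment rule in {11d}:

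1. Keep the 2-day window before the last known contact, and extend the LPV/r exclusion so that it also covers any receipt from the last contact up to ring randomisation, for any indication or in any trial.
2. Keep co-enrolment permitted, but except trials with an LPV/r arm until the day-14 outcome has been collected.

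If the full protocol already contains such rules, state them in the article's sections.

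**Cost.** Two sentences of protocol text and one screening question. A few contacts already in an LPV/r trial would not be enrolled, or participants would wait until day 14 to join one. A ban on all PEP-drug trials is not needed for this purpose and would cost more recruitment.
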